AE relationship assessment	The following categories from the MDCG 2020-10/1 Rev 1 will be used: **Not related:** Relationship to the CryoGON procedures can be excluded when: - the event has no temporal relationship with the procedure; - the serious adverse event does not follow a known response pattern to procedure and is biologically implausible; - the event involves a body-site or an organ that cannot be affected by the device or procedure; - the adverse event can be attributed to another cause (e.g. an underlying or concurrent illness/clinical condition, an effect of another device, drug, treatment or other risk factors. **Possible:** The relationship with the CryoGON procedures, is weak but cannot be ruled out completely. Alternative causes are also possible (e.g. an underlying or concurrent illness/clinical condition or/and an effect of another device, drug or treatment). **Probable:** The relationship with the CryoGON procedure seems relevant and/or the event cannot be reasonably explained by another cause. **Causal relationship:** the adverse event is associated with the CryoGON-procedure beyond reasonable doubt when: - the event is a known side effect of the any element of the procedure, including cryoneurolysis, or of similar devices and procedures; - the event has a temporal relationship with the procedures; - the event involves a body-site or organ that the procedure is applied to or the procedure have an effect on; - the adverse event follows a known response pattern to cryoneurolysis, - other possible causes (e.g. an underlying or concurrent illness/clinical condition or/and an effect of another device, drug or treatment) have been adequately ruled out; - harm to the subject is due to error in use Cases where relatedness cannot be assessed, or no information has been obtained will be classified as possible.
ADE	Any TEAE with possible, probable or causal relationship to the procedure.
SADE	Any TESAE with possible, probable or causal relationship to the procedure.
Procedural pain (tolerability)	NRS 0–10 discomfort during CryoGON; recorded immediately post-procedure.
Willingness to repeat (tolerability)	Participant-reported willingness to repeat CryoGON (yes/no/unsure) considering experienced benefits and drawbacks.

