**Secondary safety endpoints**			
Evaluate the safety of CryoGON	TE-AEs and TE-SAEs	Number of TE-SAE, TE-AE with severity ≥grad 2, and TE-AE grad 1, occurring in ≥4% or more of participants	Procedure → Week 12
Evaluate the duration of numbness in the GON innervation area following CryoGON	Days with GON-sensory deficit	Average number of days with numbness	Procedure → Week 12
Evaluate the safety of Conventional GON block	TE-AEs, TE-SAEs, ADE and SADE (treatment-emergent)	Number of TE-SAE, ADE, SADE, TE-AE with severity ≥grad 2, and TE-AE grad 1 occurring in ≥4% or more of participants	Procedure → week 4

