### Endpoints related to the open-label clinical performance of the CryoGON procedure

Open-label efficacy endpoints

The open-label efficacy of CryoGON will be evaluated based on patient-reported prospective headache diary outcomes and quality of life and patient global impression questionnaires. The migraine day endpoint variable definition is operationalized as any day with headache of minimum 4 hours duration that the participant self-identifies as a migraine, or any headache day that is successfully treated with the use of triptans and/or gepants. Patients unable to distinguish a migraine day from other headache semiologies are ineligible according to study criteria. As such, the ability of participant to identify a migraine day is part of the review at the time of inclusion and ensures that the endpoint is operationalized in a manner that adheres to the HIS’ guideline.
^
17
^ Change in quality of life will be measured with the MSQ v2.1 questionnaire at baseline and week 12. Patient global impression of change will be collected at week 8 and week 12.

Open label safety, tolerability, and feasibility endpoints

Safety will be assessed separately for CryoGON (weeks 1-12 following the CryoGON procedure) and conventional GON block (weeks 1-4 following conventional GON injection) as treatment-emergent adverse events (TEAEs) and treatment emergent serious adverse events (TESAEs), adverse device effects (ADEs) and serious ADE (SADEs). Treatment-emergent refers to all AEs events at or following initiation of the conventional GON (week 1-4) or CryoGON procedure (week 1-12), respectively. All AEs will be coded according to the Medical dictionary for regulatory activities (MedDRA) and grouped and summarised using the lowest level term (LLTs).

Severity assessment will apply the standardized grading criteria from the Common Terminology Criteria for Adverse Events (CTCAE) version 6. Casualty assessment will follow the definition of the Medical Device Coordination Group,
^
30
^ and all TEAE will be categorized as not related or possible, probable or casual related to conventional GON in week 1-4 post-procedure and the CryoGON-procedure in week 1-12 post-procedure. An adverse device effects (ADE) is defined according to ISO 14155:2020 as any adverse event related to the use of an investigational device. This is operationalised for this study as any AE that is assessed to have possible, probable or causal relationship to the CryoGON procedure.

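### The safety section ties the adverse device effect to CryoGON, yet ADEs and SADEs are also counted for the preceding GON block, so the plan conflicts on what that count contains

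*Protocol article*

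**What the plan says.** All references are to the protocol article.

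- **Endpoint for the block.** Table 4, secondary safety endpoints, has a row for the conventional GON block running from the injection to week 4. It asks for "Number of TE-SAE, ADE, SADE, TE-AE with severity ≥grad 2, and TE-AE grad 1 occurring in ≥4% or more of participants". The opening of the safety, tolerability and feasibility text likewise lists ADEs and SADEs among the measures assessed separately for CryoGON and for the block.
- **Definition of an ADE in the text.** The same section says an ADE is "defined according to ISO 14155:2020 as any adverse event related to the use of an investigational device", and continues: "This is operationalised for this study as any AE that is assessed to have possible, probable or causal relationship to the CryoGON procedure".
- **Definition in Table 3.** The ADE row reads "Any TEAE with possible, probable or causal relationship to the procedure" and the SADE row "Any TESAE with possible, probable or causal relationship to the procedure". Neither says which procedure is meant.
- **Causality scale in Table 3.** The not-related category opens "Relationship to the CryoGON procedures can be excluded when", and the possible, probable and causal categories are likewise written around CryoGON. The row ends with a default: "Cases where relatedness cannot be assessed, or no information has been obtained will be classified as possible".
- **Relatedness to the block.** Just before the ISO definition, the safety section says that treatment-emergent events will be categorised for relatedness to the conventional block in weeks 1–4 and to CryoGON in weeks 1–12.
- **Order and nature of the procedures.** Under Study outline, the block is given at visit 2 and is followed by at least 28 days of observation before CryoGON at visit 3. Under Conventional GON-block, it is an injection of lidocaine and bupivacaine.

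**The concern.** The endpoint asks how many adverse device effects the block produced, while the definition attached to that term points to a different intervention that has not yet taken place. The parent definition does not fit either: it concerns an investigational device, and the block is a drug injection.

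At stake is whether harm attributable to the block is counted as such. The trial studies the block as a possible selection step before CryoGON, so harms related to it bear on its usefulness. If two assessors, or an assessor and the statistician, follow different passages, the same event will be a block ADE for one and not for the other. This is not a detail left open for the analysis plan: the article states explicit definitions, and they disagree.

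**Working it through.** No arithmetic underlies the conflict, and the article gives no expected count or rate for this endpoint. The check sets the definitions against the visit order.

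**Step 1: do the windows overlap?** The block window is weeks 1–4, that is 4 × 7 = 28 days. CryoGON follows an observation period of at least 28 days. The block window therefore closes before CryoGON is performed.

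**Step 2: the literal reading.** Take an event clearly caused by the injection.
- The safety-section definition asks whether it is related to CryoGON.
- Table 3 excludes a relationship when there is no temporal link, or when the event can be attributed to another cause such as another drug or treatment. Both apply.
- The event is therefore not related, and not an ADE. The same holds for a serious event and the SADE count.
- The one way in is the default rule: an event whose relatedness cannot be assessed becomes possible and is counted.

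On this reading the block ADE/SADE count is empty except for unassessable cases. It would admit events about which too little is known and leave out those plainly due to the block.

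**Step 3: the alternative reading.** Take the unnamed procedure in Table 3's ADE and SADE rows as the one being tabulated. This is supported by Table 3's treatment-emergent row, which tabulates the two procedures separately, and by the safety-section sentence on relatedness to the block. The count is then the treatment-emergent events possibly, probably or causally related to the block, and nothing forces it to be empty.

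**Step 4: what each reading captures.** For a block-caused event under the Table 4 block row:

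| Event | Counted regardless of relatedness | Counted as ADE/SADE, literal reading | Counted as ADE/SADE, alternative reading |
|---|---|---|---|
| Serious | Yes, as TE-SAE | No | Yes |
| Grade 2 or higher, not serious | Yes, as TE-AE | No | Yes |
| Grade 1, in 4% or more | Yes, as TE-AE | No | Yes |
| Grade 1, in under 4% | No | No | Yes |

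Only the last row disappears altogether under the literal reading. In the other rows the event is counted but loses its related label.

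**Step 5: size of the last row.** With the target of 70 participants as denominator, the cut is 0.04 × 70 = 2.8. A grade 1 event in one participant (1/70 = 1.4%) or two (2/70 = 2.9%) falls below it; three (3/70 = 4.3%) passes. The number receiving the block may exceed 70, because some may not proceed to CryoGON and recruitment continues until the technical success set reaches its target. The cut in participants then rises in proportion.

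**The case against.** The strongest reply is that the intent is plain and the text largely delivers it. Table 3 is the article's table of endpoint variable definitions, and its ADE and SADE rows do not name CryoGON. The safety section applies ADEs and SADEs to both interventions, requires events to be categorised for relatedness to the block, and names the Medical Device Coordination Group scale for that purpose. The relatedness data will therefore exist whatever the label. Serious and grade 2 or higher block events are counted irrespective of cause.

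Most of this stands, and it limits the point. A reader might infer that the block ADE/SADE count is zero by definition. The documents do not support that: it follows from one sentence read alone, and even then the default to possible can yield a non-zero count. A reader might also infer that a safety comparison of CryoGON with the block would be biased in the block's favour. No such comparison is planned; the two are assessed separately and over windows of different length. Nor do the documents give a block event rate from which to say how many participants would be miscounted.

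The reply does not remove the conflict. In Table 3's relationship row, which directly precedes the ADE row, the unnamed procedure is shorthand for CryoGON, so reading it differently one row later is possible but not secure. The safety section's explicit operationalisation contradicts that reading. The block-relatedness sentence shows what is intended, but the categories as written out contain no wording for the block, and the ADE sentence that follows does not use that categorisation.

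**Conclusion.** The point holds as an internal contradiction in one secondary safety endpoint. Under the explicit definition in the safety section, the block ADE/SADE count is essentially empty; under Table 3's unnamed procedure together with the block-relatedness sentence, it is not. The article supports both readings and does not choose.

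The consequence is modest. On the literal reading, block-caused events lose their related label, and block-related grade 1 events below the 4% cut (one or two participants if 70 are blocked) enter no listed block count. The primary CryoGON safety endpoint, block TE-SAEs, block TE-AEs of grade 2 or higher and the prediction endpoints are unaffected. The conclusion rests on the article's wording and visit order; only the one-or-two-participant illustration assumes a denominator of 70. It is worth correcting before enrolment because a stated rule, applied as written, defeats a stated endpoint.

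**What to change.** Three aligned wording changes:

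1. In Table 3, reword the relationship categories so that they refer to the procedure under assessment: the GON block in weeks 1–4 after injection, and CryoGON in weeks 1–12 after the procedure.
2. Keep ADE and SADE for CryoGON: name CryoGON in those two Table 3 rows, and adjust the opening of the safety section so that it no longer applies the terms to the block.
3. In the Table 4 block row, replace the ADE and SADE items with TE-AEs and TE-SAEs possibly, probably or causally related to the GON block, taken from the relatedness categorisation that the safety section already requires.

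The cost is editorial. No visits or data are added; the eCRF needs a relatedness entry for block-period events, which the existing text already implies.

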## Statistical analysis

This trial is designed to evaluate if and to what degree response to conventional GON blocks predict response to CryoGON-treatment. For the primary endpoint the following hypothesis is testet:
•
**Null hypothesis (H
_0_):** There is no relationship between the degree of treatment response to conventional GON block and CryoGON treatment (regression slope (β
_1_) = 0)•
**Alternative hypothesis (H
_1_):** There is an association between the degree of treatment response to conventional GON block and CryoGON treatment (regression slope (β
_1_) ≠ 0)

### Protocol violations

Protocol violations in this study are headache diary nonadherence defined as <90% adherence and/or alterations in headache preventive treatment during trial participation. Electronic headache diary adherence will be calculated at 4-week (28 days) intervals.

### Statistical analysis

The main analysis is planned when all participants have concluded the 12-week follow-up after the CryoGON procedure and the database has been locked. A statistical analysis plan (SAP) will be finalized prior to data lock.

The full analysis set (FAS) will include all participants that received CryoGON-treatment to adhere to the intention to treat ideal and will be used for the main analysis. Two additional populations are defined for the purpose of sensitivity analyses. The per protocol set (PPS) includes participants without protocol violations. A technical success set (TSS) includes the subset of participants that fulfil the criteria for a technical successful CryoGON-treatment.

The analysis of the primary endpoint will use linear regression, with change after CryoGON as the dependent variable and change after the GON block (measured during weeks 1–4) as the main predictor. For participants who do not complete the eDiary on all days, the number of moderate-severe headache days will be calculated based on the available data and estimated for a 28-day period before calculating the change in number of moderate-severe headache days.

The key secondary outcome is defined as a ≥30% reduction in moderate to severe headache days from baseline to weeks 9–12 after CryoGON, treated as a binary response (yes/no). The corresponding GON block response is also defined dichotomously using the same threshold, assessed during weeks 1–4. The proportion of participants with ≥30% response to CryoGON will be compared between those who did and did not respond to GON block using a risk ratio with 95% confidence interval (CI).

Additional diagnostic performance measures—sensitivity, specificity, positive predictive value (PPV), and negative predictive value (NPV)—will also be calculated with 95% CI.

As this is an exploratory pilot study and the study has one specified primary endpoint, no adjustment of multiplicity is planned.

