
Key exclusion criteria include prior GON-targeted injections within 12 weeks of baseline, inability to differentiate migraine days from other headache types, or coexisting secondary headache disorders (except medication overuse headache). Patients with occipital neuralgia or neuropathy or other pain conditions that may confound evaluation of study outcomes will be excluded. Additional exclusions include unstable preventive medication regimens, prior or current occipital nerve stimulation, frequent opioid or any barbiturate use, significant psychiatric comorbidity or abnormal pain behaviour, relevant medical conditions increasing procedural risk (e.g. bleeding diathesis), and ongoing treatment site infection.

Study outline

The study will comprise four in-clinic visits and a series of structured follow-up contacts, separated by observation periods with prospective daily eDiary data collection (
Figure 2). At visit 1, eligibility will be assessed and written informed consent obtained via an electronic signature in a secure institutional digital platform (the eFORSK platform). Eligible participants will then enter a minimum 28-day baseline period, which serves both as a screening phase and to establish baseline data for endpoint assessments. A diary adherence of at least 90% (≥25 of 28 days) will be required to proceed. At visit 2, participants will be re-screened, and those meeting criteria will receive bilateral conventional greater occipital nerve (GON) blocks followed by a minimum 28-day observation period. A structured telephone call will be conducted one week after the procedure to capture any treatment-emergent adverse events and confirm scheduling for visit 3. At visit 3, eligibility will again be reassessed, including review of contraindications to CryoGON, confirmation of ≥90% diary adherence, and stable prophylactic regimens. Participants meeting criteria will undergo the CryoGON procedure (navigation-guided cryoneurolysis of the GON). Structured telephone follow-ups will be performed at weeks 1, 4, and 8, and a final in-clinic assessment will be conducted at week 12 post-CryoGON.

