## Study endpoints and endpoint variables

Endpoint variable definitions follow the International Headache Society (IHS) guideline for controlled trials of preventive treatment of chronic migraine
^
17
^ (
Table 3). The primary endpoint variable for this study is moderate to severe headache days. Several endpoints (
Table 4) are predefined to address the two main objectives of the study, i.e. assessing whether short-term response to a conventional GON block predicts subsequent response to CryoGON and evaluating the clinical performance of the CryoGON procedure.

**Table 3. T3:** Overview of endpoint variable definitions.

Variable	Definition
Moderate–severe headache day	A moderate/severe headache day is defined as a day with moderate or severe pain that lasts at least 4 hours or a day with a headache that is successfully treated by an acute headache medication.
CryoGON responder (≥30%; ≥50%)	≥30% or ≥50% reduction in moderate–severe headache days from baseline to weeks 9–12 after CryoGON.
GON block responder (≥30%; ≥50%)	≥30% or ≥50% reduction in moderate–severe headache days from baseline to weeks 1–4 after conventional GON block.
Self-reported migraine day	Any calendar day with ≥4 hours of headache and a participant-reported classification as a migraine, or any day with headache that is successfully treated with a triptan and/or gepant. For self-classification, participant are instructed to adhere to the following migraine day definition: A calendar day with a headache that lasts at least 4 hours; meets ICHD-III criteria C and D for migraine without aura (1.1), B and C for migraine with aura (1.2), or ICHD-III criteria for probable migraine (1.6); or a day with a headache that is successfully treated with a triptan and/or gepant.
Acute medication use	Number of days with use of acute medications per 28-day period. Analgesics used only for other purposes than headache treatment are not included.
Headache intensity	Maximum headache intensity is recorded on every day with headache at a 0-10 numerical rating scale.
MSQ v2.1	Migraine-Specific Quality of Life Questionnaire v2.1 (MSQ v2.1). The MSQ is copyrighted and registered with the United States Library of Congress by Glaxo Wellcome, Inc. MSQ v2.1 has undergone a formal translation process to Norwegian according to linguistic validation methodology. Permission for use will be obtained via Mapi Research trust before study initiation.

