**Primary prediction endpoint**			
Evaluate whether response to a conventional GON (cGON) block predicts response to CryoGON	Change in moderate–severe headache days	Change from baseline to weeks 9–12 after CryoGON; modelled on change after GON block (weeks 1–4) as primary predictor	Baseline; weeks 1–4 (cGON); weeks 9–12 (CryoGON)

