### Sample size

The primary scientific question is whether the response to the GON block can predict treatment outcome after CryoGON. This will be assessed both in terms of whether there is a linear association between the degree of response to GON block and response to CryoGON (primary endpoint), and whether a ≥30% response to GON block is associated a greater chance of response to CryoGON and can be used as a diagnostic test to identify those who are likely to respond to CryoGON (key secondary endpoints). Both analysis strategies are considered in the sample size calculation, together with an assessment of what are feasible recruitment numbers. Ultimately, the target samples size was set to 70 based on feasibility and the importance of the precision of estimates.

The primary analysis tests the association between change in moderate-to-severe headache days after the GON block (weeks 1–4) and change after CryoGON (weeks 9–12) using linear regression (with the null hypothesis that there is no association between the response to GON block and CryoGON, i.e. β
_1_ = 0). The proposed advantage of CryoGON is a much longer duration of treatment effect than is observed with conventional GON block. Thus, an association of 0.5 will be considered clinically meaningful, that is to say the gradient of the regression slope is 0.5, and thus for each 1-day reduction in moderate-severe headache days in weeks 1-4 after GON block, the average reduction is half a day in week 9-12 following the CryoGON-procedure. Assuming a standard deviation 5 for change in number of moderate-severe headache days from baseline, 26 participants will be sufficient to provide 80% power to detect a regression slope of 0.5 at 5% significance level.

The key secondary outcomes include a comparison of the proportion of responders to CryoGON (≥30% reduction in moderate-severe headache days) among those with and without response to GON block. This will be reported as a risk ratio (95% CI), along with sensitivity, specificity, PPV and NPV (also with 95% CI). We expect that around 40% will respond to GON block based on results from Chowdhury et al. (2021),
^
5

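### Both changes in the primary regression subtract the same baseline count, so a positive slope, about 0.5 if neither procedure works, arises without any relationship between the two responses

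*Protocol article*

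**What the plan says.** Table 4 of the protocol article defines the primary prediction endpoint as "Change from baseline to weeks 9–12 after CryoGON; modelled on change after GON block (weeks 1–4) as primary predictor" and lists a single baseline time point. Table 3 defines block response as a "reduction in moderate–severe headache days from baseline to weeks 1–4 after conventional GON block". Under Study outline there is one baseline diary period, of at least 28 days, "which serves both as a screening phase and to establish baseline data for endpoint assessments". Both changes therefore start from the same count.

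The Statistical analysis section fits a linear regression "with change after CryoGON as the dependent variable and change after the GON block (measured during weeks 1–4) as the main predictor" and names no other term. The null hypothesis, β1 = 0, is worded as "There is no relationship between the degree of treatment response to conventional GON block and CryoGON treatment". Under Sample size, "an association of 0.5 will be considered clinically meaningful", and 26 participants are said to give 80% power for that slope at the 5% level, "Assuming a standard deviation 5 for change in number of moderate-severe headache days from baseline". The target sample is 70.

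Sensitivity analyses leaves adjusted models to the SAP and gives treatment expectation, sex and age as examples. The Discussion concedes that expectation, context and individual response propensity may contribute to an association. Neither section mentions the shared baseline.

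**The concern.** When two change scores share a baseline, a participant whose baseline month happened to be unusually bad appears to improve after both procedures, and one whose baseline month was unusually good appears to worsen after both. This is regression to the mean counted twice. It gives a positive association without shared physiology or shared expectancy, so adjusting for expectancy cannot remove it.

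Two things are at stake. A significant β1 would not show that block response carries information about CryoGON response. An estimate near 0.5, which the plan would read as clinically meaningful, is also what pure diary fluctuation predicts. The ≥30% and ≥50% responder tables use the same baseline on both axes and share the problem.

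**Working it through.** **Inputs.** From the protocol article: SD of change 5 (taken for both changes), slope 0.5, two-sided 5% level, N = 26 for power, target N = 70. Not in the documents: the correlation ρ between 28-day counts, and the share of change variance that is real rather than diary noise. Both are varied below.

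**1. The plan's own figure.** With SD 5 for both changes and slope 0.5, the residual SD is 5 × √(1 − 0.25) = 4.33. A two-sided t-test of the slope with n − 2 degrees of freedom gives n = 26 and 80.6% power. The sample-size arithmetic is correct.

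**2. Slope with no effect.** Let B, Y1 and Y2 be the counts at baseline, after the block and after CryoGON, with common variance σ² and common correlation ρ. Put X = Y1 − B and Y = Y2 − B.

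- Cov(X, Y) = ρσ² − ρσ² − ρσ² + σ² = σ²(1 − ρ)
- Var(X) = 2σ²(1 − ρ)
- Slope = 0.5 for every ρ below 1

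A uniform effect of either procedure only adds a constant and leaves the slope unchanged.

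**3. Rejection of β1 = 0 with no effect (simulation, SD of change 5).** Mean slope 0.50; rejection about 77% at N = 26 and over 99% at N = 70, against a nominal 5%. The figure at N = 26 is close to the planned 80% power because the no-effect slope coincides with the planning alternative.

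**4. When part of the change is real but unrelated between procedures.** Let s be the real share of the change variance of 25. Only baseline noise is shared, so Cov(X, Y) = 25(1 − s)/2 and the slope is (1 − s)/2.

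| Real share s | Slope | False rejection, N = 70 |
|---|---|---|
| 0 | 0.50 | over 99% |
| 1/2 | 0.25 | about 55% |
| 3/4 | 0.125 | about 18% |

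**5. Departures from equal variances and correlations (no effect).**

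- Baseline error variance k times that of the post-block window: slope k/(1 + k), so 0.33 to 0.67 for k from 0.5 to 2.
- Serial decay, with the windows 1, 3 and 4 periods apart: slope (1 + ρ³)/2, so 0.51, 0.56 and 0.67 at ρ = 0.3, 0.5 and 0.7.
- Counts bounded at 0–28 and kept only if baseline is at least 8 days: slope 0.44 to 0.49, rejection 97–99% at N = 70.

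**6. Baseline added as a covariate.** The no-effect coefficient becomes ρ/(1 + ρ): 0.23, 0.33 and 0.41 at ρ = 0.3, 0.5 and 0.7. It is not zero.

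**7. The ≥30% table** (assumed baseline mean 16 and total SD 6, SD of change 5). With uniform reductions of 4 days after the block and 5 after CryoGON, 43% and 52% are responders, the risk ratio is about 1.6, PPV 67% and sensitivity about 55%, with no individual relationship between the responses. The Sample size section plans for a risk ratio of 2.67, PPV 80% and sensitivity 64%.

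**8. Separate baseline halves with independent errors.** The no-effect slope is 0.00, with about 5% rejection at N = 70.

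**The case against.** The documents limit their own inference. The study is called an exploratory pilot, the section on prediction endpoints says a significant correlation may not justify a binary decision tool, and the Discussion calls the predictive findings hypothesis-generating. That lowers the consequence of a misleading result. It does not repair the test, because none of these cautions names the shared baseline and the one adjustment the Discussion commits to, for expectation, leaves it in place.

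A second objection is that the SAP could deal with it. But the model, the null value and the meaningful slope are all fixed in this document, so this is not a detail left open.

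Three stronger readings are tempting and are not supported:

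- A reader might infer that the trial will almost surely report a false positive. That holds only if nearly all the change variance is diary noise. At a real share of three quarters the false rejection rate is about 18%, and the documents do not give the share.
- A reader might treat 0.5 as a fixed no-effect constant. It is exact only under equal variances and equal correlations.
- A reader might note that, with no effect at all, the simulated ≥30% risk ratio is about 2.8, close to the planned 2.67. That match comes from about 15% responders on each side and a PPV of about 32%, nothing like the planned table. At responder rates closer to the plan's, the ratio is about 1.6.

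**Conclusion.** The concern holds for the primary test and its benchmark. Because both changes use the same baseline count, β1 = 0 does not represent an absence of relationship, and a slope of 0.5 cannot serve as the mark of a clinically meaningful one. The no-effect slope is 0.5 under equal variances and correlations, and roughly 0.33 to 0.67 under the unequal variances and moderate serial decay examined. False rejection at N = 70 runs from over 99% with no real variation in effect to about 18% when three quarters of the change variance is real and independent. Where this trial falls in that range depends on a noise share that the documents do not give.

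The responder tables are inflated by the same mechanism, but PPV and sensitivity would stay below their planning values, so a trial without a true relationship would not look like the planned result. Nor do the documents support saying that the trial cannot answer its primary question at all: the diary data it collects allow a valid or nearly valid test. The calculation of N = 26 is arithmetically right; the fault lies in the null value and the model.

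**What to change.** Make the primary test use non-overlapping baseline days. For example, compute the block change against baseline days 1–14 and the CryoGON change against days 15–28, each scaled to 28 days, and keep H0: β1 = 0. This order should be primary: the days next to the block window then serve the other change, which offsets much of any day-to-day serial correlation. Report the shared-baseline slope descriptively only, with a statement that about 0.5 is expected with no effect. Build the responder tables the same way as a sensitivity analysis, noting that this reduces the bias without removing it (in the no-effect example the risk ratio falls from about 2.8 to 1.3). A baseline covariate alone is not enough. Restate the power and the meaningful slope for the corrected test.

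No new data are needed, but there are costs:

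- **Noise and attenuation.** With half the change variance real, Var(X) becomes 12.5 + 6.25 + 12.5 = 31.25. If true effects correlate 0.8, the slope is 0.8 × 12.5/31.25 = 0.32.
- **Power.** At N = 70 in that setting it is about 77% for a true correlation of 0.8, 39% for 0.5 and 17% for 0.3.
- **Residual inflation.** With strongly serially correlated daily headache (assumed daily autocorrelation 0.8–0.97), simulated false rejection was about 7–19%; at 0.8–0.9 the planned analysis gave about 98%. Swapping the halves did worse, up to about 50%.

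A longer baseline, which the 28-day minimum allows, would reduce the first two costs but adds diary time.
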